#### Aim 2: To determine how affordability, accessibility, and awareness affect sustained use of LPG in adopter households

To study sustained use, we will focus on group 1 (LPG adopters) of our sample. SUMS will be used to measure duration of use (a measure of maintenance) of clean cooking technologies of the study participants. We will use SUMS for both the LPG stoves and traditional cookstoves in a randomly selected subset of 100 households from group 1 (LPG adopters) [31]. We will receive SUMS data on: 1) duration of use of these stoves; 2) extent of use of LPG stoves relative to traditional stoves. We will monitor the use of these stoves for 12 months. SUMS data will be recorded and downloaded every two weeks from each of the 100 households by a trained field person. We will download data using a probe connected to a laptop computer via USB port. Files will be uploaded to our database management system (RedCap). Informed consent will be obtained from the households to continue using the stoves as they do routinely. SUMS will provide continuous data on stove usage in 100 households. For analysis purposes, we will also dichotomize this data as: 1) exclusive LPG users, and 2) stackers. Households using LPG at least 80% of the cooking duration during the monitoring period of 12 months will be characterized as exclusive LPG users. This metric will facilitate comparison of the results of this study with other LPG adoption studies currently underway in different parts of the world [32]. We will use a SUMS data log sheet to record the biweekly SUMS data on sustained use. In addition, we will undertake a follow up survey in these 100 households. During the monitoring period (post enrollment of households) status of 3As in the habitations might change. This requires a follow up survey at the end of 6 and 12 months of the monitoring period. Follow up survey will have questions pertaining to the 3As, focused on the monitoring period. Follow up questionnaires and SUMS data collection will be administered to 100 LPG adopter households.

#### Aim 3: To evaluate the relative influence of gender networks on LPG adoption in rural households

Personal social networks of individuals in communities influence awareness levels, which in turn drive adoption, implementation, and maintenance of stoves [39]. Implementation of health interventions are impacted by the personal networks of men and women in the households [38, 39]. Both men and women play a critical role in adopting, implementing, and maintaining cleaner cooking technologies like LPG [39]. Thus, it is critical to assess the personal networks of study participants to ascertain how they influence (or get influenced by) decisions related to making a fuel switch. To generate personal network data, we will use a personal network survey to probe the women (primary cook) and the adult male (or primary male decision maker) of 100 households each in the case and control groups. This approach is novel in understanding the role of gender dimensions and the peer effects impacting their fuel choice. Personal social networks, or egocentric networks, focus on the structure and composition of the networks surrounding a target individual [40]. We will use a well-established ego-centric network survey instrument to measure personal networks of men and women. The gendered network data will be collected as follows: 1) the survey will begin with three name generator questions to prompt identification of individuals who give advice, socialize, and support the respondent. 2) After eliciting the network members, a second set of questions will be performed to evaluate the strength of the connections (tie strength) between the respondent and the individuals identified by the respondent; 3) subsequently, the strength of the connections between the network members identified will be probed; 4) finally, characteristics of the network members identified will be solicited (e.g., their demographics, income, household size, and cooking habits).

### Research instruments

A summary of the research instruments is provided in Table 2. Each of the research instruments will be drafted in English and will be translated into Telugu (local language of the region in India).

**Table 2 Tab2:** Data collection instruments

Conceptual domains	Aims	Research instrument	Method or Measure	Data source	Sample size
Adoption of LPG	Aim 1	Adoption questionnaire	Structured interview	Households: women	LPG adopter households (case): 255; Non-LPG adopter households (control): 255
Sustained use of LPG	Aim 2	SUMS	Stove temperature monitoring	Households: LPG and traditional stoves	LPG adopter households (case): 100
Sustained use of LPG	Aim 2	Follow up questionnaire	Structured interview	Households: women	LPG adopter households (case): 100
Personal social networks of LPG adopters and non-LPG adopters impacting adoption of LPG	Aim 3	Social network survey questionnaires for women and men	Structured interview	Households: women, men	LPG adopter households (case): 100 Non-LPG adopter households (control): 100

### Data analysis

#### Aim 1: To understand how rural LPG adopters vary from other rural households on factors of affordability, accessibility, and awareness of LPG

We will conduct preliminary univariate and bivariate data analyses. The categorical outcome variable for aim 1 (adoption of LPG: yes/no) will be regressed on the predictors (3As) recorded from the adoption questionnaire. We will have two levels of data from the household adoption questionnaire covering information on the 3As: level 1) household level characteristics such as income, women’s financial autonomy, household size, or caste; and level 2) community level characteristics such as LPG cylinders’ home delivery facility, presence of paved roads, government promotion campaigns, or distance of LPG distribution centers from the habitation. Depending on the values of intra class correlation (ICC) coefficient (if higher than the accepted norm of 5%), we will conduct additional analyses. We will use these two levels of data to conduct a multilevel regression modeling (using R version 3.0.3) with habitations as grouping variable, to predict these higher-level influences of 3As on adoption of LPG among rural households. We will also analyze the interaction effect of 3As on LPG adoption.

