We use a multistage random sampling to select households in these rural habitations. To facilitate sample selection, we develop an exhaustive list of habitations (and households in these habitations) with four key variables: 1) distance to nearest LPG distribution center; 2) dominant caste of the habitation; 3) number of households in each habitation; 4) presence of LPG adopters in these habitations. A multistage sample selection process will be conducted using the following steps in their respective order:
**Sample of habitations:** We will use stratified random sampling to select the list of villages for the study. The selection criteria are:

*Proximity to the nearest LPG distribution center:* Based on the distance from the nearest LPG refilling and distribution center, we divide the exhaustive list of habitations (i.e. habitations population list) in two sub-groups: near to the center and far from the center, by taking a median split of the distance of the habitation from the LPG distribution center.
*Dominant caste of the habitation:* We divide the habitations population list into three sub-groups: General Caste, Other Backward Castes (OBC), and Scheduled Castes/Scheduled Tribes (SC/ST).

These two stratifying variables and their subgroups will lead to six distinct strata (2subgroups*3subgroups). We will divide the habitations population list across these six distinct strata. We will select a total sample of 35 habitations from these six distinct strata. Table 1 shows an indicative list of the six distinct strata that will be used to select the final 35 habitations.2.We have data on the number of LPG adopters and non-adopters from each of these selected habitations. We will use quota sampling to select households from each of these habitations. We will randomly select 255 LPG adopter households (case) from these 35 habitations. Subsequently, we will select as many non LPG adopter households (control) as we have LPG adopters (case) across each of the habitations. This will ensure a case control design in every habitation, with a control to case ratio as 1, and a total sample size of 510 households.

**Table 1 Tab1:** Exhibit list of stratified random sample of habitations

Strata	Proximity to LPG distribution centers	Dominant caste
1	Near	General
2	Near	OBC
3	Near	SC/ST
4	Far	General
5	Far	OBC
6	Far	SC/ST

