### Study participants (*N* = 510; 255 from each group)

The inclusion criteria for the study participants are: rural household with an adult male and female member (>18 years age), woman respondent who is able to provide consent for the study, the woman respondent is the primary cook of the house, senior most male respondent (or primary male decision maker in the household) who is able to provide consent for the study, women respondent residing in the household for the last 12 months, women respondent plans to reside in the household for at least 12 months from the date of enrollment for the study. An additional inclusion criterion for case group (LPG adopter households) is: household has received the first LPG cylinder in the last 12 months from the date of enrollment for the study.

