### Data collection

#### Aim 1: To understand how rural LPG adopters vary from other rural households on factors of affordability, accessibility, and awareness of LPG

A structured household adoption questionnaire will be used to record data on social, economic, and demographic characteristics. Women (primary cook) from each household will be the respondent for this questionnaire. In addition to household demographic characteristics, the questionnaire will record data pertaining to the 3 significant drivers impacting LPG adoption: affordability, accessibility, and awareness (3As) of LPG. The categorical outcome variable for aim 1 will be adoption of LPG at the time when data collection is undertaken for the household. Candidate variables on affordability include household income, upfront costs to acquire LPG, access to bank loans, facility of payment in installments for LPG purchase and refill, regularity of income (in past 12 months), and women’s financial autonomy. Candidate variables on accessibility include distance of habitations and households from LPG distribution centers, presence of paved roads to LPG distribution centers, and nature of LPG cylinders’ home delivery system. Candidate variables for awareness include government promotion campaigns, local self-government *(Gram Sabha)* awareness drives, and participation of women in self-help groups. In addition, we will capture data on how organizations at the community level, including government entities, and LPG distributors shape household adoption and sustained use of LPG. Candidate organizational factors are irregular supply and bureaucratic hurdles to apply for LPG, which will be assessed from the perspective of households. Key control variables that will be recorded are caste, household size, months of LPG ownership (in case group), educational status of household head, and free availability of biomass. This adoption questionnaire for aim 1 will be administered to all 510 households immediately after their enrollment in the study.

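### Aim 1 reads household answers as community-level predictors, but 1:1 selection within each habitation leaves only within-habitation differences for such items to show

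*Protocol article*

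**What the plan says.** **Source of the data.** The Aim 1 data analysis section says "We will have two levels of data from the household adoption questionnaire covering information on the 3As". It lists "level 2) community level characteristics such as LPG cylinders’ home delivery facility, presence of paved roads, government promotion campaigns" and distance of the distribution centers from the habitation. These enter a multilevel regression with habitation as the grouping variable, which is meant to show higher-level influences of the 3As on adoption.

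**Respondent.** The Aim 1 data collection section says "Women (primary cook) from each household will be the respondent for this questionnaire". Irregular supply and bureaucratic hurdles are organizational factors "which will be assessed from the perspective of households". Table 2 lists no habitation survey or distributor record. The article gives no rule for turning several answers from one habitation into one value.

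**Timing.** A case qualifies if the "household has received the first LPG cylinder in the last 12 months from the date of enrollment for the study" (Study participants). The exposure questions therefore follow adoption.

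**Selection.** Within each sampled habitation, as many non-adopters as adopters are taken: "This will ensure a case control design in every habitation, with a control to case ratio as 1" (Sampling and recruitment). The same section describes a list of habitations "with four key variables: 1) distance to nearest LPG distribution center", and says that adopter and non-adopter counts are held for each selected habitation.

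**Limitations.** Recall bias is conceded for Aim 1. The text suggests that the large sample of households close to one another may lessen it.

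**The concern.** A community characteristic has one value per habitation; this instrument yields one value per respondent. An adopter has dealt with the distributor, the delivery arrangement and perhaps the promotion, so she may describe them differently from a non-adopter next door. If those answers enter the model as level 2 predictors, a significant coefficient for delivery, roads or campaigns would be read as an effect of what the habitation offers.

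The RE-AIM section says the protocol examines individual and organizational levels together, and the Discussion directs the results to government LPG distribution policy. Differences between neighbours could thus be reported as evidence on supply.

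The selection rule adds a second difficulty. Measuring the community factor correctly would not recover its effect, because the sample is balanced on it by construction.

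**Working it through.** **1. The plan's own figure.** The sample size is based on income: n = 2 × [2199.26 × (1.960 + 0.842) / 545.35]² = 255.3 per group, with power 79.95% at 255. It reproduces the stated 255 and 80%, but has no bearing on this point.

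**2. A factor shared by the habitation.** Let habitation h contribute m_h cases and m_h controls, and let T_h be 1 if the factor is present and 0 otherwise.

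- Exposed cases = Σ m_h T_h, and exposed controls are the same sum. Call it A, with B = 255 − A unexposed in each group.
- Odds ratio = (A × B) / (B × A) = 1.00, whatever the true effect on adoption.

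As a check, 35 habitations were laid out as 10 with 8 pairs and 25 with 7 pairs (80 + 175 = 255), with 2,000 simulated datasets per scenario. The odds ratio of the true factor was 1.00 in every dataset. The habitation mean of the household answers had zero correlation with adoption.

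The multilevel model does not alter this: the adopter share is one half in every habitation, so there is no between-habitation variation in the outcome to explain. Once household covariates are added, a habitation coefficient need not be exactly zero, but it is still tied to the selection ratio and does not estimate a community effect.

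**3. The household's own answer.** The inputs here are assumptions, not document figures. The factor is present in 50% of habitations and has no effect on adoption. Reported prevalence is p = 0.5 × sensitivity + 0.5 × false-positive rate, in cases (p1) and controls (p0). The odds ratio is [p1/(1−p1)] / [p0/(1−p0)]. The chance of two-sided p < 0.05 is Φ[(|p1−p0| − 1.96 × SE0)/SE1], with SE0 pooled, SE1 unpooled and 255 per group.

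| Sensitivity, cases / controls | False positives | p1 / p0 | Odds ratio | Chance of p < 0.05 |
|---|---|---|---|---|
| 90% / 80% | 0 | 0.45 / 0.40 | 1.23 | 21% |
| 80% / 60% | 0 | 0.40 / 0.30 | 1.56 | 66% |
| 90% / 60% | 0 | 0.45 / 0.30 | 1.91 | 94% |
| 90% / 90% | 10% | 0.50 / 0.50 | 1.00 | no bias |
| 95% / 85% | 10% | 0.525 / 0.475 | 1.22 | 20% (simulated 10%) |
| 95% / 75% | 10% | 0.525 / 0.425 | 1.50 | 62% (simulated 65%) |
| 95% / 65% | 10% | 0.525 / 0.375 | 1.84 | 93% (simulated 96%) |

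The formula ignores the balance within habitations, which makes the unadjusted test conservative when reporting is equal (simulated rejection 0.2%). The chances are therefore approximate.

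The range also depends on prevalence. With the factor in 80% of habitations, sensitivities 95% and 75% and 10% false positives, p1 = 0.78, p0 = 0.62 and the odds ratio is 2.17.

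**The case against.** **Perception is partly the intended construct.** The Study design section defines awareness to include perception, and the organizational factors are openly household-reported. A woman's report of a campaign is a fair measure of her household's awareness. This stands, and it supports treating the answer as a household variable. It does not support labelling it a community characteristic.

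**Neighbours can truly differ.** The data collection section names distance of households as well as habitations, and delivery may also vary by household. This stands too. A reader might infer that any non-null coefficient must be a reporting artefact; the documents do not support that, because real household differences can produce it as well.

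**Habitation distance may come from the sampling list.** The analysis section does not rule this out, so it cannot be said that the plan ignores the list. No comparable source is described for roads, delivery or campaigns.

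**Differential reporting is not documented.** Correct: its existence and size are assumed here. It is also less plausible for roads and distance, which are easily observed, than for campaigns.

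**The study calls itself exploratory and concedes recall bias.** This tempers the consequence. It does not answer the point, because a larger sample does not reduce reporting that differs by adopter status; it makes a spurious result more likely to reach significance.

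**One value per habitation would only yield a null.** This is the strongest objection and it is right. A reader might infer that measuring the item once per habitation would recover the community effect. Under the 1:1 selection it would not, so the fix must say so.

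**Conclusion.** The point holds in a limited form. The article takes its level 2 items from individual answers given after adoption, and reads them as higher-level influences. Under equal selection in every habitation, a non-null main effect for such an item reflects within-habitation differences, whether in reporting or in real household circumstances. It is not evidence about what the habitation is supplied with.

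The marginal odds ratio of 1.00 for a truly shared factor follows from the selection rule and needs no assumption beyond that rule being achieved. The spurious odds ratio of about 1.2 to 1.9 is an illustration. It assumes reporting gaps of 10 to 30 points, a factor present in half the habitations and false-positive rates of 0 or 10%. With equal reporting there is no bias.

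Two stronger readings are not supported: that adopters and non-adopters are known to report differently, and that a null coefficient for a well-measured habitation factor would show supply to be irrelevant.

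**What to change.** In the Aim 1 data analysis section:

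1. Give each level 2 item one value per habitation: distance from the sampling list; for roads, delivery and campaigns, one record per habitation or the habitation mean of the household answers. Enter each household's deviation from that value as a separate level 1 variable, labelled household-reported access or awareness.
2. Do not interpret the level 1 deviation as a community or supply effect. Note that it may mix real household differences with reporting influenced by adoption.
3. State that main effects of habitation-level factors on adoption cannot be estimated under 1:1 selection within habitations, and that a null habitation coefficient is not evidence of no supply effect. Limit level 2 use in the case-control sample to cross-level interactions. For main effects, use the adopter and non-adopter counts already held for each habitation.

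**Cost.** The change is to analysis and interpretation. The habitation mean needs no new data; a direct record adds a few items for each of 35 habitations. An analysis of counts would rest on about 35 units, so its precision would be modest. The main price is that the study gives up its claim to estimate community-level main effects from the case-control sample.

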### Sampling and recruitment

We will undertake a case control study in the rural habitations of Thambalpalle and Peddamandyam mandals (block) in Chittoor district of Andhra Pradesh state in India [27]. Our implementing partner, Foundation for Ecological Security (FES) has extensive field experience working in this region and we will leverage their expertise and understanding of social, economic, and demographic characteristics of the households in these habitations.

We will select an equal number of case and control households for this proposed study (control to case ratio will be 1:1). We will select a sample size of 255 households each for case (LPG adopter households) and control (LPG non-adopter households). A total sample size of 510 households at a 95% confidence level (alpha = .05) will provide a power of 80% to this study at a control to case ratio of 1. This computation assumed that the populations mean difference in monthly income was 545.35 India National Rupee (INR), and the common within-group standard deviation was 2199.26 INR per month. In the absence of previously published studies on rural income in this region, where the study is to be undertaken, the power computation was conducted using a baseline income data from another recently concluded NIH funded R21 (WUSTL IRB ID# 201207016) randomized controlled trial (RCT) on cookstoves. This study will be conducted in the same region where the RCT was undertaken. To calculate the sample size, we used the Power and Precision 4 software. The criterion for significance (alpha) was set at 0.05. The test was 2-tailed, and so an effect in either direction will be interpreted. With the proposed sample size of 255 each for case and control group, the study will have power of 80% to yield a statistically significant result. It is also assumed that this effect size is reasonable; an effect of this magnitude could be anticipated in this field of research. On average, a study of this design would enable us to report the mean income difference with a precision of 95% confidence level.

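### Controls are matched 1:1 within habitation, but neither the 5% ICC trigger nor the random-intercept model can register that matching, so household-level odds ratios in aim 1 are pulled toward 1

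*Protocol article*

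**What the plan says.** Sampling and recruitment, on the number of habitations: "We will select a total sample of 35 habitations from these six distinct strata". After 255 adopter households have been drawn, "Subsequently, we will select as many non LPG adopter households (control) as we have LPG adopters (case) across each of the habitations". The stated purpose is: "This will ensure a case control design in every habitation, with a control to case ratio as 1".

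Data analysis, Aim 1, says that adoption (yes/no) "will be regressed on the predictors (3As) recorded from the adoption questionnaire". It describes household-level and community-level predictors and then makes further work depend on an ICC: "Depending on the values of intra class correlation (ICC) coefficient (if higher than the accepted norm of 5%), we will conduct additional analyses". The next sentence, which carries no condition of its own, describes a multilevel regression "with habitations as grouping variable", meant to capture the higher-level influences of affordability, accessibility and awareness (the 3As). Interactions among the 3As are also planned.

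The analysis text does not mention the within-habitation quota, a conditional or stratified analysis, or a fixed habitation term.

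**The concern.** Equal numbers of cases and controls in each habitation amount to frequency matching on habitation. Matching makes the controls resemble the cases on whatever goes with habitation. If the analysis then ignores the matching factor, the odds ratio for any exposure related to that factor is biased toward 1.

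The plan decides whether habitation matters by looking at an ICC. For adoption, the sampling has already fixed that ICC, so it says nothing about how strongly adoption truly clusters. The two parts of the plan do not fit together.

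The household-level effects are at stake. They are what aim 1 can estimate well, on the full sample of 510, and the Limitations section says the findings will supply effect sizes for a larger study. Attenuated estimates would carry into that study's planning.

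**Working it through.** **Inputs from the protocol.** 255 cases and 255 controls; 35 habitations; ratio 1:1 in every habitation; ICC threshold 5%; income difference 545.35 INR; SD 2199.26 INR; two-sided alpha 0.05; power 80%. The protocol gives no figure for how strongly any predictor clusters by habitation, so those values are assumptions shown as a range.

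**1. The plan's own figure.** n per group = 2 × (1.960 + 0.842)² × (2199.26/545.35)² = 2 × 7.85 × 16.26 ≈ 255.3, or 256 rounded up. Power at 255 per group is 0.7995. The stated sample size reproduces and is not in dispute.

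**2. The ICC of adoption under the quota.** Mean habitation size is m = 510/35 = 14.57. Every habitation has a case share of 0.5, so the between-habitation mean square is 0. The within-habitation mean square is 510 × 0.25/(510 − 35) = 0.268.

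ICC = (0 − 0.268)/(0 + 13.57 × 0.268) = −1/13.57 = **−0.074**.

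The quota would have to fail badly before 5% was passed:

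| SD of case share across habitations | ICC |
|---|---|
| 0 (quota met) | −0.074 |
| 0.10 | −0.030 |
| 0.15 | 0.026 |
| 0.20 | 0.102 |

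**3. If the multilevel model is run regardless.** Habitation-matched data were simulated (255 + 255 households, 35 habitations, 40 runs per setting). Assumptions: habitation effects with SD 0.7 on the logit scale, correlated 0.3 with the habitation mean of the predictor. For a true odds ratio of 2.0:

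| Between-habitation share of predictor variance (assumed) | Unmatched | Random intercept | Conditional logistic |
|---|---|---|---|
| 5% | 1.954 | 1.954 | 2.019 |
| 10% | 1.892 | 1.892 | 2.001 |
| 30% | 1.679 | 1.679 | 2.039 |
| 50% | 1.477 | 1.477 | 2.053 |

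Without covariates the random-intercept variance was estimated at zero throughout. With the household predictor in the model, the residual ICC averaged at most 0.0006 across all settings tried (true odds ratios 1.5, 2 and 3) and exceeded 5% in no run.

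**4. Size of the bias at a true log odds ratio of 0.40 per SD.** A hand approximation shows where it comes from. Let s be the between-habitation share of the predictor's variance. Matching removes the between-habitation contrast, so the case-control difference in means is about 0.40 × (1 − s). The unmatched model divides this by the full variance of 1, giving 0.40 × (1 − s). If community-level covariates absorb half of the between-habitation variance, the divisor falls to 1 − s/2, giving 0.40 × (1 − s)/(1 − s/2).

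| s (assumed) | Unmatched, by hand | Unmatched, simulated | Half explained, by hand | Half explained, simulated |
|---|---|---|---|---|
| 5% | 0.38 | 0.39 | 0.39 | 0.40 |
| 20% | 0.32 | 0.33 | 0.36 | 0.36 |
| 30% | 0.28 | 0.29 | 0.33 | 0.33 |

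Conditional logistic regression gave 0.40 to 0.41 throughout.

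**5. Habitation-level factors.** A habitation with k cases contributes its distance, road, delivery and campaign values k times to the cases and k times to the controls. The two distributions are identical, so the coefficient of such a factor on its own is zero whatever its true effect on adoption. With household predictors alongside, it only absorbs part of their between-habitation variation. Conditioning on habitation removes these factors altogether. Neither approach estimates their main effects.

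**The case against.** **The reading of the trigger is uncertain.** The multilevel sentence can be read as unconditional, and the protocol does not say which variable's ICC is meant. A reader might infer that habitation certainly stays out of the model, or that no ICC could ever pass 5%. The text does not support that: the result in step 2 is for the ICC of adoption with the quota met. This part of the objection stands, but it does not rescue the plan. If the trigger is skipped, or fires on some other variable's ICC, the model that follows is the random-intercept fit of step 3, which equals the unmatched one.

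**The bias may be small.** The planned model carries community-level 3As and controls such as caste and household size, which take up some of the between-habitation variation. This also stands: at an assumed 30% clustering the estimate rises from 0.29 to 0.33 if half is explained. The recovery is partial, and at 5% clustering there was little to recover.

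**Clustering is not documented.** A reader might infer that income, education and women's autonomy are known to differ between habitations. The protocol supports this only for caste, through its dominant-caste strata, and for distance, its other stratifier. The shares used above are assumptions.

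**False positives.** A reader might also infer that a 5% cut-off inflates the type I error for habitation-level factors, as it can in an ordinary cluster sample. That does not apply here. The quota balances such factors between cases and controls, and in a simulation of this design the nominal 5% test of such a factor rejected in 0% of runs.

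**Exploratory study, condensed article.** The study calls itself exploratory, and the full plan is not shown. This limits the severity. The quota and the analysis rule are nevertheless both stated in the article, and they conflict there.

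**Conclusion.** The point holds. With the quota met, the ICC of adoption is −0.074 by construction, and on either reading of the analysis text the fitted model is in effect an unmatched regression of matched data. The direction of the bias, toward 1, is consistent for household predictors that cluster by habitation.

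Its size is not known from the protocol. On a true log odds ratio of 0.40, the loss without community covariates is about 2.5% (0.39), 17.5% (0.33) and 27.5% (0.29) for assumed clustering of 5%, 20% and 30%. If community covariates explain half of the between-habitation variance, it is about 0%, 10% and 17.5%. A predictor that hardly varies between habitations is barely affected.

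The conclusion assumes that the 1:1 quota is broadly achieved in each habitation. It does not question the sample size or the choice of a case-control design. It should be fixed: the bias is avoidable at the analysis stage, but its size is uncertain and the study is exploratory.

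**What to change.** In Data analysis, Aim 1:

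- Remove the ICC trigger.
- State that household-level 3A effects and their interactions, including household-by-community interactions, are estimated conditional on habitation by conditional logistic regression stratified on habitation. Habitation fixed effects or a within-between model would serve the same purpose.
- State that main effects of habitation-level factors (distance, roads, home delivery, campaigns) on adoption cannot be estimated under the within-habitation quota, either by this model or by the one now planned. Amend the objective of predicting higher-level influences accordingly.

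The cost is a few sentences and a standard R routine, with no extra data. Giving up habitation-level main effects is not a cost of the change, because the sampling quota has already removed them.
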